## 5 Study Design Overview

We will conduct an observational cohort study to evaluate the VE of Moderna COVID-19 vaccine in preventing COVID-19 diagnosis and severe COVID-19. Vaccine exposure, COVID-19 outcomes, and covariates will be identified from EHR, as described in Section 7 below. All individuals who receive Moderna COVID-19 vaccine from December 2020 to December 2021 and meet eligibility criteria specified in Section 6.1 below will be included in the study (“vaccinated”, hereafter). The unvaccinated comparator cohort will comprise individuals who have not received Moderna COVID-19 vaccine or any other COVID-19 vaccine as of the index date of their matched vaccinated individual (see Section 6.2 for details on index date) and who meet eligibility criteria specified in Section 6.1 below. Unvaccinated individuals who subsequently receive Moderna COVID-19 vaccine may contribute person-time to both unvaccinated and vaccinated cohorts. Individuals will be followed up through EHR for occurrence of COVID-19 outcomes until the end of the study period (December 31, 2023 for final analysis), or censoring events (termination of KPSC membership allowing for a 31-day gap, death, receipt of a COVID-19 vaccine).

Six interim analyses and a final analysis will be conducted. For the first and second interim analyses, unvaccinated individuals will be randomly selected and n:1 matched to vaccinated individuals by age, sex, and race/ethnicity (if sample size allows), and will be assigned an index date based on the vaccination date of their matched vaccinated individual. For subsequent interim analyses and the final analysis, the number of eligible unvaccinated individuals in the KPSC population may be insufficient for individual matching; if so, frequency matching will be employed. In all analyses, efforts will be dedicated to identifying and adjusting for potential confounders. Cox proportional hazards regression will be used to estimate unadjusted and adjusted HRs. VE (%) will be estimated as  $(1 - \text{adjusted HR}) \times 100$ . Propensity score analyses with inverse probability of treatment weighting (IPTW) will be considered for final analyses.

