### 7.3 Other Variable Definitions

Other variables (Table 3) will be identified from EHR and considered in analyses when feasible and appropriate as covariates or stratification variables.

Table 3. List of possible covariates

|                                                                                                  | Categories                                                                                |
|--------------------------------------------------------------------------------------------------|-------------------------------------------------------------------------------------------|
| Variables to be assessed at index date (Day 0)                                            |                                                                                           |
| Age at index date, years                                                                         | 12-17, 18-44, 45-64, 65-74, 75+                                                           |
| Sex                                                                                              | Female, Male                                                                              |
| Race/Ethnicity                                                                                   | Non-Hispanic White, Non-Hispanic Black, Non-Hispanic Asian, Hispanic, Other/Unknown       |
| Month of index date                                                                              | By calendar month                                                                         |
| Socioeconomic status                                                                      |                                                                                           |
| Medicaid                                                                                         | Yes, No                                                                                   |
| Neighborhood median household income                                                             | To be determined based on variable distribution                                           |
| Medical center area                                                                              | MC1, MC2, MC3, ...                                                                        |

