1. The distribution of covariates will be reviewed. Some categories of a categorical variable with small sample sizes may be redefined or combined into one category.
2. The association of baseline covariates with exposure will be assessed. We will use standardized difference to assess the balance of covariates between exposed and unexposed cohorts. Unlike p-values, for which magnitude is highly related to sample size, standardized difference is a unified approach to quantifying the magnitude of difference between groups regardless of sample size, where an absolute value less than 0.1 is considered a negligible difference. Potential confounders will be determined by absolute standardized difference (ASD) >0.1.
3. All potential confounders from Step 2 will be included in the analyses. Steps 1 and 2 will be repeated for the 2-dose cohort and the 1-dose cohort. Matching variables (age, sex, race/ethnicity and index date), which are considered important risk factors, will be kept in the

adjusted model for possible imbalance on matching variables due to loss to follow-up or subgroup analysis (e.g., by baseline comorbidities).

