## 9 Sample Size and Power Estimation

Power calculations depend on Moderna COVID-19 vaccine implementation, uptake, and the number of individuals meeting criteria for comparable vaccinated and unvaccinated cohorts.

We estimate that a total of 80,000 individuals will receive 2 doses of Moderna COVID-19 vaccine from December 2020 through March 2021, assuming 80% series completion (first interim analysis). We estimate an incidence of 30 COVID-19 diagnoses per 1,000 unvaccinated adult KPSC members during an average 4-month follow-up period (accounting for possible censoring). We expect to have >99.9% power to detect a VE of 70%, with various sample sizes in the unvaccinated group (Table 4), using a 2-sided test with  $\alpha=0.007$  (0.05 adjusted for 6 interim analyses and 1 final analysis). The calculation was performed using SAS software package (version 9.4) PROC POWER procedure.

Table 4. Power calculations for 1st interim analysis of Primary Objective 1 for various sample sizes and vaccine effectiveness estimates

| Sample Size Ratio
(Vaccinated vs
Unvaccinated) | Incidence rate in
unvaccinated group
(cases/1000 persons) | VE (%)
(reduction rate) | Power |
|------------------------------------------------------|-----------------------------------------------------------------|----------------------------|-------|
| 1 vs 0.5                                             | 30                                                              | 90                         | >.999 |
|                                                      | 30                                                              | 80                         | >.999 |
|                                                      | 30                                                              | 70                         | >.999 |
| 1 vs 1                                               | 30                                                              | 90                         | >.999 |
|                                                      | 30                                                              | 80                         | >.999 |
|                                                      | 30                                                              | 70                         | >.999 |
| 1 vs 5                                               | 30                                                              | 90                         | >.999 |

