|                                                      | 30                                                              | 80                         | >.999 |
|                                                      | 30                                                              | 70                         | >.999 |

For the first interim analysis of Primary Objective 2, we estimate an incidence of 2 COVID-19 hospitalizations and 0.3 deaths per 1,000 unvaccinated adult KPSC members during an average 4-month follow-up period. We expect to have >99.9% power to detect a 70% VE against COVID-19 hospitalizations, with various sample sizes in the unvaccinated group (Table 5).

Table 5. Power calculations for 1st interim analysis of Primary Objective 2 for various sample sizes and vaccine effectiveness estimates

| Sample Size Ratio
(Vaccinated vs
Unvaccinated) | Incidence rate in
unvaccinated group
(cases/1000 persons) | VE (%)
(reduction rate) | Power |
|------------------------------------------------------|-----------------------------------------------------------------|----------------------------|-------|
| 1 vs 0.5                                             | 2                                                               | 90                         | >.999 |
|                                                      | 2                                                               | 80                         | >.999 |
|                                                      | 2                                                               | 70                         | >.999 |
| 1 vs 1                                               | 2                                                               | 90                         | >.999 |
|                                                      | 2                                                               | 80                         | >.999 |
|                                                      | 2                                                               | 70                         | >.999 |
| 1 vs 5                                               | 2                                                               | 90                         | >.999 |
|                                                      | 2                                                               | 80                         | >.999 |

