## 10.2 Cohort design

The matched variant cohort will be developed in the same way as the matched cohort assembled for the primary analyses (Section 6.1 and Section 6.2, Study Objectives 1-2), using the same 2-dose Moderna COVID-19 vaccine exposure described in Section 7.1. Because Moderna COVID-19 vaccination began in December 2020 at KPSC, but archiving and WGS of SARS-CoV-2 positive specimens did not begin until March 2021, we will modify the matched cohort from the primary analysis to set index dates to begin no earlier than February 14, 2021 (14 days prior to March 2021). The cohort eligibility criteria will be applied based on the modified index date.

Baseline characteristics of the 2-dose Moderna COVID-19 vaccine cohort will be described and compared between the vaccinated and unvaccinated groups, as for the primary analyses above (Section 8.2). For each VOC or VOI, separately, the incidence of a specific VOC or VOI for the 2-dose vaccinated and unvaccinated individuals will be calculated by dividing the number of individuals with an incident COVID-19 diagnosis with a specific VOC or VOI by the total number of person-years. The person-years for an individual in the cohort will be the time from 14 days after the index date to the date of event of interest, death, disenrollment (allowing for a 31-day gap), end of follow-up (February 28, 2022), or receipt of a dose of any COVID-19 vaccine, whichever comes first. The event date is the date of the first incident COVID-19 diagnosis with a specific VOC or VOI after the index date. In addition, the follow-up time for individuals with an incident COVID-19 diagnosis for which the variant is unknown (i.e., sequencing unsuccessful or not sequenced) or different from the specific variant of interest will be censored on the date of the COVID-19 diagnosis. We will calculate incidence rates of specific VOCs and VOIs, unadjusted and adjusted HRs, and VEs, as described for the primary analyses above (Section 8.3)

If sample size allows, similar analyses will be conducted for VOCs and VOIs associated with COVID-19 hospitalization. Hospitalizations include hospitalized death, but there may be insufficient sample size to assess VE against COVID-19 hospitalized death by variant. Since the cohort analysis will only be conducted at the end of study (February 2022), no adjustment for multiple testing is needed.

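### Keeping index month in the adjusted Cox model, on its natural reading, does not fully remove the calendar imbalance that censoring at vaccination creates; the yearly durability estimates are the most exposed

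*Protocol*

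**What the plan says.** Section 6.2 gives each comparator the index date of the matched vaccinee. Under frequency matching it reproduces the vaccinees' distribution of index dates. Either way, balance is set at the index date only.

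Section 5 ends follow-up at the end of the study "or censoring events (termination of KPSC membership allowing for a 31-day gap, death, receipt of a COVID-19 vaccine". This applies to both arms: a first dose for comparators, a further dose for vaccinees. Section 10.2 repeats the rule for the variant cohort.

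Section 7.3, Step 3 anticipates the resulting imbalance and states a remedy: "Matching variables (age, sex, race/ethnicity and index date), which are considered important risk factors, will be kept in the". The same sentence then names where these variables are kept and why: "adjusted model for possible imbalance on matching variables due to loss to follow-up or subgroup analysis". Table 3 carries the variable as "Month of index date", by calendar month.

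Section 8.3 fits Cox models without and with these covariates. Section 8.4 (Objectives 12-13) estimates VE by follow-up year after the index date. Section 10.2 counts person-time from 14 days after the index date and takes over the same models: "unadjusted and adjusted HRs, and VEs, as described for the primary analyses above (Section 8.3". No section names index-date strata, conditioning on matched sets, or a calendar time axis for the cohort models.

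**The concern.** COVID-19 incidence depends on the calendar date, which is index date plus time since index. Matching aligns the two arms at time zero. Comparators then leave when they are vaccinated, and Section 4.1 shows that eligibility opened in calendar phases through May 2021. Vaccinees leave later and on another schedule, at a further dose. At a given time since index, the people still at risk in the two arms therefore come from different mixes of calendar dates.

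Step 3 names this kind of imbalance and offers index date in the model as the cure. If that term is a proportional main effect, the cure is partial, and part of the shared rise and fall in incidence passes into the hazard ratio. With 500,000 to 1,000,000 vaccinees expected (Section 9), sampling error is small, so even a modest bias can harm interval coverage. In the durability analyses the bias can change with follow-up year and so imitate waning.

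**Working it through.** **1. The plan's own figures.** The protocol gives no figure for calendar bias. Its power inputs are sound: "We estimate that a total of 80,000 individuals will receive 2 doses of Moderna COVID-19 vaccine from December 2020 through March 2021", "we estimate an incidence of 2 COVID-19 hospitalizations and 0.3 deaths per 1,000 unvaccinated adult KPSC members", and alpha 0.007 ("0.05 adjusted for 6 interim analyses and 1 final analysis"; 0.05/7 = 0.00714).
- Table 5, deaths, 1 vs 1, VE 90%: p0 = 0.0003, p1 = 0.00003, n = 80,000 per arm. The difference is 0.00027, the standard error is √[(0.0003 + 0.00003)/80,000] = 0.0000642, and z for 0.007 two-sided is 2.697. Power = Φ(0.00027/0.0000642 − 2.697) = Φ(1.51) = 0.93, as stated. VE 80% and 70% give 0.81 and 0.62, also as stated.
- Section 10.3, variant cohort, by Freedman's formula: (1.96 + 0.84)² × (1.2/0.8)² = 7.85 × 2.25 = 17.7, so 18 events, of which 15 are unvaccinated, as stated.

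These figures agree, but none bears on calendar confounding.

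**2. Why a main effect is not enough.** Let λ(c) be the shared hazard on calendar date c, m the index date and t the time since index. The true hazard is λ(m + t)·exp(β·vaccinated). The model with index month as a covariate is h0(t)·exp(β·vaccinated + γ_m). The two agree only if log λ(m + t) = a(t) + γ_m for all m and t, which requires log λ to be linear in calendar time. A wave is not. Stratifying replaces h0(t) with a separate h0m(t) for each index period, so the condition is no longer needed.

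**3. Assumptions for size.** All curves are assumed. Everyone has the same underlying risk and censoring is non-informative, so any departure from the true VE is calendar bias.
- Set A: 500,000 per arm; uniform index dates; comparator uptake peaking in April-May 2021 at 1.2% per day or half that; boosters from 180 days after dose 2; Delta-like wave peaking mid-August 2021 (SD 30 days).
- Set B: weekly cells of time since index, index week and arm; comparator vaccination scaled from 0 to 1.5 times a central curve; booster censoring 0 or 6% per week.
- Set C: a further weekly-cell fit for the Delta-like wave.

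**4. Checks on the mechanism.** With no censoring at vaccination, the month covariate gives VE within 0.3 point of truth (set B). With constant incidence the bias is essentially nil (set A). Both follow from step 2.

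**5. Adjusted VE (%) with index month as a covariate**

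| Analysis | True 80% | Other true VE |
|---|---|---|
| First interim | 80.0 (B) | bias about 0.2 point or less (A) |
| Third interim | 80.0 to 80.7 (B) | |
| Final, overall | 79.2 to 80.1 (B) | 70%: 69.6 to 69.9 (A); 50%: 48.0 to 50.1 (B) |
| Variant cohort, Delta-like wave | 78.0 to 79.0 (A); 78.4 to 80.2 (B); 78.1 to 79.2 (C) | 50%: 46.5 to 50.3 (B); 45.7 to 48.0 (C) |
| Variant cohort, spring 2021 wave | 79.1 to 79.6 (A); 79.5 to 80.0 (B) | |
| Variant cohort, January 2022 wave | 80.2 to 80.4 (B) | 50%: 50.4 to 50.7 (B) |

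In set A a true VE of 0 gives an adjusted HR of 1.05 to 1.08 for the Delta-like wave. The error is roughly multiplicative on the HR, so it costs more VE points when VE is lower: 1 − 0.20 × 1.08 = 78.4%, but 1 − 0.50 × 1.08 = 46.0%. Narrow-wave stress cases at a true 80% give 76.7 to 80.2.

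**6. Durability (set B), constant true VE 50%**

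| Comparator vaccination | Booster censoring | Year 1 / 2 / 3 |
|---|---|---|
| 0.5× | none | 49.8 / 49.5 / 48.8 |
| 0.5× | 6% per week | 49.8 / 48.2 / 45.9 |
| 1× | none | 49.4 / 48.9 / 47.4 |
| 1× | 6% per week | 49.3 / 46.7 / 43.0 |
| 1.5× | none | 49.1 / 48.2 / 45.8 |
| 1.5× | 6% per week | 48.4 / 44.8 / 39.7 |

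Month strata return 49.9 to 50.2 in every row.

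**7. After the change.** Index-week strata or a calendar time axis recover the true VE exactly. Month strata were within about 0.2 point in sets A and C. In set B they were within 0.8 point at a true 50% and 1.6 points at a true 0.

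**The case against.** The strongest objection is that the protocol never says index date is a proportional term. Section 7.3 allows the Table 3 variables to serve as covariates or as stratification variables, the time axis of the overall models is not stated, and Section 11 schedules a separate statistical analysis plan that may settle both. That stands in part: the proportional reading is the natural one, not a stated rule. It does not dispose of the point. Step 3 names the problem and states a remedy that, read plainly, does not do its stated job. For the variants, Section 10 is itself headed as the statistical analysis plan, and it was added after the separate plan's June 2021 due date.

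The size is also modest. The month term already removes most of the error where that error is large: for a January 2022 wave at a true 50%, unadjusted VE reaches 62.7 and adjusted VE is 50.4 to 50.7. The variant cohort is conditional on similar testing and sequencing proportions, and Objective 16 is also addressed by the test-negative design, which matches specimen date within 10 days. All of this stands.

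A reader might infer that the unadjusted hazard ratio is itself a defect. It is not: Section 5 defines VE from the adjusted HR, and the unadjusted figure is reported beside it.

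**Conclusion.** The point holds as a weakness in a stated method, with a cheap remedy. On the natural reading, index month in the adjusted Cox model leaves some calendar confounding once both arms are censored at vaccination. The overall primary VE is little affected. The effect is more material for a Delta-like wave in the variant cohort, and can be largest in Objectives 12-13, where the bias may grow with follow-up year.

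Three stronger readings are not supported:
- That epidemic waves are credited to the vaccine and inflate VE. The adjusted error mostly runs toward the null and varies in sign.
- That the variant cohort is always the worst case. The yearly durability estimates can be hit harder.
- That the primary conclusion is at risk. The shifts in the overall estimate are too small for that.

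Every bias figure rests on assumed incidence, uptake and booster curves. What does not depend on them is the algebra: a main effect is sufficient only if log incidence is linear in calendar time.

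**What to change.** In Section 7.3 Step 3, Section 8.3, Section 8.4 (Objectives 12-13) and Section 10.2, replace the retention of index date as a model term with wording such as: the adjusted Cox models will be stratified by calendar week of index date, or by month where weekly strata are too sparse, with vaccination and the remaining covariates as regression terms. An alternative is calendar date as the time axis with delayed entry at day 14. Weekly strata or the calendar axis are preferable to monthly strata, which can leave a small residual error.

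No new data are needed. The cost is a slight loss of precision: with month strata in set A, the standard error of the log HR went from 0.0482 to 0.0485 in the variant scenario and stayed at 0.0092 in the final primary analysis. Sparse strata in small subgroups may need merging.

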## 8 Statistical Analysis for Study Objectives 1-15

### 8.1 Analysis Plan

For Primary Objectives 1-2, interim analyses will be conducted every 3 months in the first year, beginning in July 2021 (Figure 1). The first interim analysis will include all vaccinated individuals who are accrued in the first ~3 months of the study (December 2020 to March 2021) and followed for at least 3 months after completion of the second dose. The second and third interim analyses will be performed in October 2021 and January 2022 with cumulative accrual from December 2020 to June 2021 and December 2020 to September 2021, respectively. Interim analyses will be performed every 6 months in the second and the third year. Matching of the unvaccinated comparator cohort to the vaccinated cohort will be conducted separately at each of the first 4 interim analyses, such that each analysis will have a different unvaccinated cohort. However, the unvaccinated cohort will remain fixed beginning with the 4th interim analysis through the final analysis (Primary Objectives 1-2 and Secondary Objectives 1-15), which will include all vaccinated individuals accrued in 2021, with follow-up through December 2023. No data lags are applied for the first 3 interim analyses, but a 3-month data lag is applied starting with the 4th interim analysis. The removal of the data lag for the first 3 interim analyses will permit more rapid generation of results. Without the 3-month data lag, some events reported through claims may be missed, leading to an underestimation of incidence rates. However, we expect the proportion of claims to be non-differential in the vaccinated and unvaccinated cohorts.

Figure 1. Analysis Plan for Study Objectives 1-15

[figure not shown]

